### Sample collection

2.5

Venous blood samples (2 mL) will be collected from eligible neonates into gel tubes containing a clot activator, adhering to institutional safety protocols and standard procedures for biological sample handling. Blood collection will be performed within the first 24 h of life, followed by a second sample at 48–72 h, contingent upon clinical stability and the presence of an indication for additional routine laboratory investigations. In neonates with longer hospitalizations, a third sample may be obtained on day 7 of life.

### Sample processing

2.6

Following blood collection, samples will be immediately transported to the central laboratory for processing. Centrifugation will be performed using an Orto Alresa Microcen 23 centrifuge, operated at 4,000 revolutions per minute (rpm) for 10 min, under room temperature conditions. After centrifugation, the separated serum will be transferred into a single, pre-labeled Eppendorf tube for each participant. All samples will be stored at −50 °C until further analysis. No aliquoting will be performed and all samples will remain under uniform storage conditions throughout the study duration to minimize pre-analytical variability. Upon completion of recruitment, stored serum samples will undergo batch analysis to quantify selected biomarkers associated with surfactant deficiency and pulmonary injury. Quantitative evaluation will be conducted using commercially available sandwich enzyme-linked immunosorbent assay (ELISA) kits validated for use in human serum. To safeguard the novelty of this research, the specific biomarkers evaluated will be disclosed following validation and publication of study findings.

To ensure participant anonymity and maintain blinding during laboratory analyses, each sample will be labeled using a unique alphanumeric code. The coding format will be as follows: “CS” for neonates born to mothers with cholestasis or “FC” for those born to mothers without liver disease, followed by the first initial of the neonate's last name, an optional number for multiple births (1, 2, or 3 for twin or triplet order), a gender identifier (5 for male, 6 for female), and the date of birth in the format DDMM. For example, a male neonate, twin 1, born to a mother with cholestasis, with the last name Niculae, and born on 21st of May, would be assigned the code CSN152105. This code will be recorded on both the primary collection tube and the Eppendorf storage tube. The code list will be securely maintained by the principal investigator, and laboratory personnel responsible for biomarker analysis will remain blinded to the clinical identity and group assignment of each participant.

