### Data collection and management

2.7

Data will be prospectively collected using standardized forms specifically developed for the CHOLE-RESP study. Maternal variables will include demographic characteristics (age and body mass index at delivery), obstetric history, biochemical parameters (serum bile acid concentrations, transaminase levels), and pregnancy-related complications (gestational diabetes mellitus, hypertensive disorders, risk of maternal-fetal infection). Information regarding mode of delivery, use of ursodeoxycholic acid therapy and relevant perinatal events (e.g., meconium-stained amniotic fluid) will also be recorded. Neonatal data will include sex, birthweight, gestational age at delivery, Apgar scores at 1, 5, and 10 min, need for resuscitation, diagnosis of RDS and indicators of respiratory morbidity such as surfactant administration, timing and dosing of surfactant therapy, need for mechanical ventilation or non-invasive respiratory support, oxygen supplementation (FiO₂ requirements), severe respiratory complications including pneumothorax, pulmonary hemorrhage and persistent pulmonary hypertension, NICU admission, duration of hospitalization and neonatal mortality.

Each participant will be assigned a unique anonymized code (as previously described), which will be applied to all clinical records and biological samples. The correspondence between personal identifiers and study codes will be stored separately in a password-protected file accessible exclusively to the principal investigator. Data will be entered into a secure electronic database, with regular cross-verification against source documents to ensure data integrity. Laboratory personnel performing biomarker analyses will remain blinded to group assignment. All data collection and management procedures will comply with institutional ethical guidelines and data protection regulations.

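### The sample code begins with the exposure group and is written on every tube, so the labelling as described contradicts the stated laboratory blinding; the code is also not guaranteed unique

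*Protocol article*

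**What the plan says.** Protocol article, section 2.6 (Sample processing), gives the purpose of the code: "To ensure participant anonymity and maintain blinding during laboratory analyses, each sample will be labeled using a unique alphanumeric code". It then sets out the format. The first two characters are "CS” for neonates born to mothers with cholestasis or “FC” for those born to mothers without liver disease". After them come the initial of the surname, "an optional number for multiple births (1, 2, or 3 for twin or triplet order"), and "a gender identifier (5 for male, 6 for female), and the date of birth in the format DDMM". The worked example, CSN152105, has the group prefix in place.

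On where the code appears: "This code will be recorded on both the primary collection tube and the Eppendorf storage tube". On who may know the group, the section ends by saying that the code list stays with the principal investigator and that "laboratory personnel responsible for biomarker analysis will remain blinded to the clinical identity and group assignment of each participant".

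Section 2.7 (Data collection and management) repeats the commitment: "Laboratory personnel performing biomarker analyses will remain blinded to group assignment". It also applies the same participant code to clinical records as well as samples. The Discussion lists laboratory blinding among the features that strengthen internal validity.

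**The concern.** The code is the only blinding device that the article describes, and it displays the item to be concealed. Restricting access to the code list does not help, because the prefix gives the group without the list. Staff who had never been told what the letters mean could still sort the tubes into two sets, and the article itself publishes the meaning.

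The biomarker comparison is a co-primary objective, it drives the sample size, and it is framed with a directional hypothesis (section 2.3). An ELISA reading is quantitative, but people still decide which runs to repeat, which values to treat as outliers and which haemolysed or low-volume samples to reject. The Discussion expects such samples. If the group can be read when those decisions are made, they can differ by group, and this cannot be undone after the assay.

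Uniqueness is a lesser matter. Two neonates who share group, surname initial, sex, and day and month of birth would share a code. Because the code also labels the clinical records, a duplicate could attach a biomarker result to the wrong clinical outcome.

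**Working it through.** **Plan's own figure.** The one design figure in the article is a power of 0.952 for 66 exposed and 132 unexposed (one-sided t-test, effect size 0.5, α = 0.05). The noncentral t distribution with 196 degrees of freedom and noncentrality 0.5 × √(66 × 132 / 198) = 3.32 gives 0.9516, so the figure reproduces. Nothing below alters it.

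**Blinding.** This part needs no arithmetic. Section 2.6 makes four statements:
1. The code serves to maintain blinding in the laboratory.
2. Its first two characters are the exposure group.
3. It is written on the primary tube and on the storage tube.
4. Laboratory personnel do not know the group.

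Statements 2 and 3 place the group on the object that the analyst handles. Statement 4 could then hold only through a further step, such as relabelling or masking before the assay. The article describes none, and statement 1 names this code as the device.

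**Uniqueness.** Inputs from the document:
- 66 exposed and 132 unexposed (section 2.3).
- Recruitment from 1 October 2024 to 31 December 2027 (section 2.1), which is 3 + 36 = 39 months. Every day and month therefore recurs three or four times.
- The code elements listed in section 2.6, with no year and no serial number.

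Assumptions: birth dates uniform over 365 days, the sexes equally likely, all neonates singletons, and L equally likely surname initials. The documents give no surname distribution, so L is varied.

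The prefix separates the groups, so duplicates arise only within a group. Possible pairs are 66 × 65 / 2 = 2,145 and 132 × 131 / 2 = 8,646, in total 10,791. Cells per group are C = L × 2 × 365. Expected duplicate pairs = 10,791 / C. The chance of at least one duplicate in a group of n is 1 − ∏(1 − i/C) for i = 0 to n − 1, and the two groups are then combined.

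| L | Shared-initial probability 1/L | C | Expected pairs | Chance of at least one |
|---|---|---|---|---|
| 26 | 0.038 | 18,980 | 0.57 | 43% |
| 20 | 0.050 | 14,600 | 0.74 | 52% |
| 15 | 0.067 | 10,950 | 0.99 | 63% |
| 10 | 0.100 | 7,300 | 1.48 | 77% |

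For L = 26 the group figures are 10.7% and 36.7%, so 1 − 0.893 × 0.633 = 43%. With a more skewed distribution (frequency proportional to 1/rank over 23 letters, also assumed), simulation gives 28.6% and 74.8%, so 1 − 0.714 × 0.252 = 82%.

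Treating everyone as a singleton overstates these figures slightly, because the birth-order digit separates a twin or triplet from a singleton. Uneven birth dates would push them up.

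**The case against.** The strongest reply is that this is a condensed article. It commits twice to blinded analysts, and it does not say that the person who labels or centrifuges a tube also runs the ELISA. A masked worklist or a relabelling step could sit in a laboratory manual that is not shown. This reply stands against the stronger reading that a reader might draw, namely that blinding does not exist and every tube is unblinded at assay. The text does not establish that. It does not rescue the passage as written, because the article sets out the coding format in full and presents it as the blinding measure.

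A second reply is that batch-run commercial ELISA leaves little room for judgement, and that haemolysed or insufficient samples must be documented. That narrows the risk without removing it, and it means that bias should not be claimed as shown. The respiratory distress and surfactant co-primaries do not depend on laboratory blinding at all.

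Third, the duplicate-code estimate rests on an assumed distribution of initials, and about one pair among 198 neonates could be caught against the key or by the source-document checks in section 2.7. This stands. It is why the range is wide and the point is secondary.

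Finally, a reader might infer from the missing time field, and from serum being "transferred into a single, pre-labeled Eppendorf tube for each participant", that samples at 24 h, 48–72 h and day 7 will be confused or merged. The documents do not support this. The article does not say that nothing else is on the label, the sentence sits beside a statement that serum is not aliquoted and can mean one undivided tube per draw, and such label detail is commonly left to a fuller document. It merits a clarification only.

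**Conclusion.** The labelling procedure as described reveals the exposure group to anyone handling the tubes and contradicts the blinding statements in sections 2.6 and 2.7 and the Discussion. This follows from the text alone and rests on no assumption. What it puts at risk is the biomarker co-primary, through discretionary decisions on samples and runs. The documents give no basis for a size of bias, and none is claimed.

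Secondarily, the claim that the code is unique is not secured by its format. Under the stated assumptions the chance of at least one duplicate runs from 43% to 77%, or about 82% with a more skewed distribution of initials. That would be an administrative correction if it stood alone.

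The blinding point should be settled before any assay. The Discussion reports 54 exposed neonates already recruited and preliminary biomarker analysis starting at 60 participants.

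**What to change.** Replace the tube code with a neutral, unique random or serial accession number for each tube. Hold group, identity and sampling time only in the principal investigator's restricted key, which already exists. Have someone outside the assay team relabel the tubes already stored before any ELISA run, including the preliminary analysis at 60 participants, and describe that step in section 2.6. If relabelling or masking is already practised, stating it there would remove the contradiction.

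Deleting only the CS/FC prefix would not be enough. All 198 neonates would then share one set of codes, with 198 × 197 / 2 = 19,503 possible pairs, so expected duplicates would rise to 19,503 / 18,980 = 1.0 up to 19,503 / 7,300 = 2.7 under the same assumptions. The participant identifier in the clinical database should be unique as well, for instance by a serial number.

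As a clarification, state that there is one storage tube per sampling time.

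The cost is a wording change, labels and a one-off relabelling of frozen tubes. At the reported count that is at most 54 × 3 = 162 tubes from exposed neonates, plus those from any controls enrolled by then. No additional patients, procedures or change in sample size are needed.

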### Data collection and management

2.7

Data will be prospectively collected using standardized forms specifically developed for the CHOLE-RESP study. Maternal variables will include demographic characteristics (age and body mass index at delivery), obstetric history, biochemical parameters (serum bile acid concentrations, transaminase levels), and pregnancy-related complications (gestational diabetes mellitus, hypertensive disorders, risk of maternal-fetal infection). Information regarding mode of delivery, use of ursodeoxycholic acid therapy and relevant perinatal events (e.g., meconium-stained amniotic fluid) will also be recorded. Neonatal data will include sex, birthweight, gestational age at delivery, Apgar scores at 1, 5, and 10 min, need for resuscitation, diagnosis of RDS and indicators of respiratory morbidity such as surfactant administration, timing and dosing of surfactant therapy, need for mechanical ventilation or non-invasive respiratory support, oxygen supplementation (FiO₂ requirements), severe respiratory complications including pneumothorax, pulmonary hemorrhage and persistent pulmonary hypertension, NICU admission, duration of hospitalization and neonatal mortality.

Each participant will be assigned a unique anonymized code (as previously described), which will be applied to all clinical records and biological samples. The correspondence between personal identifiers and study codes will be stored separately in a password-protected file accessible exclusively to the principal investigator. Data will be entered into a secure electronic database, with regular cross-verification against source documents to ensure data integrity. Laboratory personnel performing biomarker analyses will remain blinded to group assignment. All data collection and management procedures will comply with institutional ethical guidelines and data protection regulations.

### Statistical analysis

2.8

Statistical analysis will be performed using JASP 0.19.2. Frequency analysis will be performed using contingency tables. Group differences in the incidence of RDS and the need for surfactant therapy will be assessed using the chi-squared test or Fisher's exact test, where expected cell counts are less than five. Differences in mortality will be evaluated descriptively using odds ratios (ORs), and if event frequency permits, time-to-event analysis may be considered. In addition, time-to-event outcomes such as time to first surfactant dose, time to intubation and time to second surfactant administration will be analyzed using Kaplan–Meier curves and compared using the log-rank test, with Cox regression models applied where appropriate.

Serum biomarker levels indicative of lung injury will be compared between groups at each time point using the Student's *t*-test for normally distributed data or the Mann–Whitney *U* test when normality is not assumed. To assess longitudinal trends in biomarker levels, repeated-measures ANOVA or linear mixed-effects models will be employed, depending on data distribution and completeness. For non-parametric repeated data, the Friedman test may be used. Normality and homogeneity of variances will be tested using the Shapiro–Wilk and Brown-Forsythe tests, respectively. A significance level of 0.05 will be used for all analyses. For normally distributed biomarker data, standardized mean differences between groups will be reported as Cohen's d and Glass's delta. To account for potential residual confounding, gestational age at birth, matched during enrollment, will additionally be included as a covariate in relevant statistical models and stratified analyses may be performed to explore outcome differences across gestational age subgroups.

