### Sample size calculation

2.3

An *a priori* power analysis was performed using JASP (version 0.19.2) to estimate the required sample size for detecting a between-group difference in biomarker levels with adequate statistical power. Assuming a one-sided independent samples *t*-test, a medium effect size (Cohen's |*δ*| = 0.5), a Type I error rate (*α*) of 0.05 and a target power (1−*β*) of 0.95, the analysis indicated that a minimum of 66 participants in the ICP-exposed group and 132 in the unexposed group would be required to achieve an actual power of 0.952.

These parameters were selected to align with the study's directional hypothesis that intrahepatic cholestasis of pregnancy is associated with poorer respiratory outcomes and higher biomarker levels. A 2:1 unexposed-to-exposed ratio was adopted to address the lower expected incidence of neonates with maternal ICP, providing greater statistical precision while also enhancing generalizability and minimizing bias, without placing disproportionate demands on recruitment. Also, the higher power threshold of 0.95 was chosen to ensure adequate sensitivity for detecting clinically meaningful biomarker differences, which represent a novel co-primary objective and a central component of the study's design.

This configuration provides robust power to detect moderate effect sizes over 0.5 with high reliability, acknowledging that smaller effects (|*δ*| ≤ 0.25) are associated with a substantially reduced probability of detection. Accordingly, a minimum of 198 neonates will be enrolled to meet the sample size requirements established by the power analysis.

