### Eligibility criteria

2.4

Participants will be enrolled into either the exposed or unexposed group based on predefined eligibility criteria. The exposed group will consist of neonates born to mothers with a recent diagnosis of intrahepatic cholestasis of pregnancy, defined by serum bile acid concentrations exceeding 10 µmol/L within seven days prior to delivery. Furthermore, written informed consent needs to be obtained at least one hour prior to birth. No minimum gestational age at delivery is imposed and eligible neonates must be either born at the study location or transferred to the unit from another neonatal facility within the first 24 h of life. Exclusion from this group will apply in instances where informed consent is not provided, where no serum bile acid measurement is available in the specified time frame or where measured bile acid levels are below 10 µmol/L.

The unexposed group will comprise neonates born at the same institution to mothers without a known history of hepatic disease prior to or during the index pregnancy. Controls will be matched according to gestational age at birth, birthweight and sex. Consistent with the ICP-exposed group, informed consent must be obtained a few hours before delivery. Maternal administration of ursodeoxycholic acid at any point during pregnancy, regardless of dosage or timing, will constitute an exclusion criterion for this group, as it may suggest subclinical hepatic dysfunction.

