Several design features strengthen the internal validity and feasibility of this study. By including both term and preterm neonates, the study captures the full clinical spectrum of ICP-related deliveries and enables stratified analyses. Also, given the multifactorial nature of neonatal respiratory distress syndrome, statistical models incorporate established clinical risk factors, including gestational age, sex and perinatal infection, to minimize residual confounding and avoid overestimation of the effect of bile acid exposure. Biological samples are collected at defined time points and handled according to standardized protocols, with laboratory personnel blinded to group allocation. The decision to integrate all sampling into clinically indicated procedures minimizes patient risk and reinforces ethical compliance.

Additionally, preliminary retrospective data from our center (June 2020 to December 2024) identified 66 preterm infants born to mothers with ICP among 1,078 preterm births. Although the overall incidence of RDS was not consistently increased, these neonates demonstrated greater respiratory morbidity, with higher requirements for invasive ventilation, non-invasive CPAP and surfactant, as well as longer duration of respiratory support compared with controls. It should be noted that the relatively low number of ICP cases observed retrospectively reflects previous limitations in clinical practice, as bile acid testing was not routinely performed in Romania and often not covered by the public health system. Since October 2024, however, systematic testing for symptomatic mothers and updated obstetric management have been implemented in our institution, already resulting in 54 ICP-exposed neonates recruited within 14 months of prospective enrollment, confirming the feasibility of the study, with control recruitment scheduled to begin after one year. Technical validation of the ELISA kits has been performed in advance and preliminary biomarker analysis will commence once 60 participants are enrolled, with interim results expected to be presented at an international neonatology conference.

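### The primary comparisons use unadjusted two-sample tests that ignore the matching and the siblings, and the Discussion claims covariates (sex, perinatal infection) that section 2.8 does not name

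*Protocol article*

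**What the plan says.** Section 2.2 sets three primary objectives: RDS incidence, need for surfactant, and serum biomarker profiles. Section 2.8 gives the tests. For the two binary outcomes: "Group differences in the incidence of RDS and the need for surfactant therapy will be assessed using the chi-squared test", with Fisher's exact test when expected counts are small. Biomarkers are compared at each time point by Student's t or Mann-Whitney.

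On adjustment, section 2.8 adds that "gestational age at birth, matched during enrollment, will additionally be included as a covariate in relevant statistical models", and allows stratification by gestational age. It names Cox regression for time-to-event outcomes and linear mixed-effects models for biomarker trends. It names no regression model for RDS or surfactant need as yes/no outcomes.

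The Discussion describes the analysis differently: "statistical models incorporate established clinical risk factors, including gestational age, sex and perinatal infection".

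Two design features bear on independence. Section 2.4: "Controls will be matched according to gestational age at birth, birthweight and sex"; whether matching is individual or by frequency is not said. Section 2.6 provides in the sample code for "an optional number for multiple births (1, 2, or 3 for twin or triplet order"), so siblings enter as separate participants. The sizing in section 2.3 uses the same independence assumption: "Assuming a one-sided independent samples *t*-test".

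**The concern.** This is an observational comparison, so the error bars and the control of confounding rest on the analysis. The tests named for the primary outcomes treat the planned 198 infants as unrelated and cannot carry a covariate.

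- **Matching.** Infants alike in gestational age, birthweight and sex have similar risks, all the more because section 2.4 sets no minimum gestational age. A test that ignores this uses too large a standard error.
- **Siblings.** Twins and triplets share a mother and therefore an exposure status, and their outcomes are correlated. A test that ignores this uses too small a standard error.
- **Confounding.** Where it succeeds, matching balances its own three factors. Perinatal infection is not matched, and no test named for a primary comparison can adjust for it. The Discussion nevertheless presents adjustment for it as a strength.

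A reader of the Discussion would take the main RDS and surfactant results to be adjusted. Under section 2.8 as written, they would not be.

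**Working it through.** **1. The plan's own figure.** Inputs from section 2.3: one-sided independent-samples t-test, d = 0.5 ("a medium effect size"), "a Type I error rate (*α*) of 0.05", groups of 66 and 132. The noncentrality is 0.5 × √(66 × 132 / 198) = 0.5 × √44 = 3.317 with 196 degrees of freedom. Power is 0.9516, which matches the stated 0.952. The next smaller 1:2 design, 65/130, gives 0.949, so 66/132 is the minimum. The arithmetic is right, for independent infants. Section 2.8 does not say whether its 0.05 is one- or two-sided; I report two-sided size unless stated.

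**2. Matching ignored, biomarkers.** Assumed: individual 1:2 sets and within-set correlation ρ. The true variance of the group difference is (1 − ρ) × (1/66 + 1/132) in SD² units; the unmatched test uses (1/66 + 1/132). Its true size is therefore 2 × [1 − Φ(1.96 / √(1 − ρ))].

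| ρ | 1.96 / √(1 − ρ) | true size |
|---|---|---|
| 0.2 | 2.191 | 0.028 |
| 0.5 | 2.772 | 0.006 |

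Power at the design effect d = 0.5 with ρ = 0.4: the unmatched SE is 0.1508 and the true SE is 0.1508 × √0.6 = 0.1168.
- Unmatched: Φ((0.5 − 1.96 × 0.1508) / 0.1168) = Φ(1.75) = 0.96.
- Matched: Φ(0.5 / 0.1168 − 1.96) = Φ(2.32) = 0.99.

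**3. Matching ignored, RDS.** Simulation of 66 sets of 1:2. Assumed: baseline logit −1.4 (risk about 20% when sets do not vary), a normal set effect on the logit scale, and an odds ratio of 3 within sets. Chi-squared is compared with a Mantel-Haenszel test stratified by set (for a set with m events, expectation m/3 and variance m(3 − m)/9).

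| set-level SD | size, chi-squared | size, matched | power, chi-squared | power, matched |
|---|---|---|---|---|
| 0 | 0.048 | 0.049 | 0.91 | 0.91 |
| 1 | 0.034 | 0.049 | 0.85 | 0.88 |
| 2 | 0.014 | 0.048 | 0.61 | 0.78 |
| 3 | 0.005 | 0.049 | 0.34 | 0.67 |

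Repeated runs agree within about 0.02. Compare across a row; the fall down a column also reflects the changing marginal effect.

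**4. Siblings ignored.** Assumed: a share t of infants in twin pairs, the same in both groups, and sibling correlation ICC. The design effect is 1 + t × ICC, and the naive size is 2 × [1 − Φ(1.96 / √DE)].

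| t | ICC | DE | naive size | power at 66/132 (one-sided, effective n) | size to restore |
|---|---|---|---|---|---|
| 0.05 | 0.3 | 1.015 | 0.052 | 0.949 | 67/134 |
| 0.20 | 0.5 | 1.10 | 0.062 | 0.934 | 73/146 |
| 0.30 | 0.8 | 1.24 | 0.078 | 0.907 | 82/164 |

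One-sided, naive size runs from 0.051 to 0.070.

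**5. Covariates named in each place.**

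| Factor | Section 2.8 | Discussion |
|---|---|---|
| Gestational age | yes, in some models | yes |
| Sex | not named | yes |
| Perinatal infection | not named | yes |

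**The case against.** **The plan is not without models.** Section 2.8 allows Cox regression for time to first surfactant dose and mixed models for biomarker trends, and both can carry covariates. That stands. It does not reach the yes/no comparison of RDS or surfactant need, nor the comparison of biomarkers at each time point, where the tests named are unadjusted.

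**A reader might infer a contradiction on gestational age.** There is none: section 2.8 plans it as a covariate in some models and allows strata. Only sex and perinatal infection are unreconciled, and sex is at least a matching factor.

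**Individual matched sets are an inference.** This is correct. The figures in steps 2 and 3 apply only if matching is individual. Under frequency matching the remedy is adjustment for the matching factors, which is needed either way.

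**The effects may be small.** Partly right. Ignoring matching does not create false positives, and at the design effect the biomarker power loss is slight (0.96 against 0.99). A reader might point to larger losses at smaller effects, but section 2.3 sizes for 0.5 and already concedes weak power at 0.25 or below. The sibling inflation is modest over most of the assumed range. The RDS loss is real only if risk varies strongly between sets.

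**A reader might infer that antenatal corticosteroids go unrecorded**, since section 2.7 does not list them. That list condenses study forms that are not shown, so the inference is not supported.

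**Conclusion.** The point holds and should be fixed, but it is not fatal to the study. As written, all three primary outcomes are compared by tests that ignore the matching and the siblings and cannot adjust, and the Discussion credits the analysis with sex and perinatal infection as covariates that section 2.8 does not contain.

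The direction of the error is mixed. Over the assumed ranges, ignoring matching takes two-sided size down to about 0.028 to 0.006. For RDS at an odds ratio of 3 it costs little power with modest between-set variation (0.85 against 0.88) and much more with large variation (0.61 against 0.78). Ignoring siblings takes size up to about 0.052 to 0.078. The documents give no twin share, sibling correlation, within-set correlation or RDS rate, so no net figure can be stated.

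Two stronger readings fail. The omissions do not both inflate false positives, because they pull against each other. And the sample size is not miscalculated: 66/132 reproduces under its stated assumptions.

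**What to change.** Name one adjusted model per primary outcome in section 2.8 as the primary analysis:

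- **RDS and surfactant need:** logistic regression.
- **Biomarkers:** linear regression on a suitable scale.
- **Covariates in each:** exposure, the matching factors (gestational age, birthweight, sex) and perinatal infection.
- **Siblings:** standard errors clustered by mother, or a random effect for mother.
- **Matching:** state whether it is individual or by frequency. If individual, record the set number and account for the set.

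Make the covariate lists in section 2.8 and the Discussion agree. Keep chi-squared, Fisher, t and Mann-Whitney as descriptive.

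The cost is low. Section 2.7 already lists sex, birthweight, gestational age and risk of maternal-fetal infection; the additions are a mother identifier in the analysis file and, if needed, a set number. The drawback is a slightly more complex model, and the number of events limits how many covariates the logistic models can carry. The change is best made before the preliminary biomarker analysis that the Discussion plans at 60 participants, so that the models are not chosen with results in view.
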